### Additional secondary analysis

Statistical methods mentioned in the statistical analysis will be applied according to the characteristics and distribution of the data.
Compare the secondary outcome between the two groups;Subgroup analysis will include:
Septic shock (yes/no)Stage of AKI on the enrolment day (no AKI, AKI, chronic kidney disease without receiving RRT regularly)intravenous volumes of the assigned crystalloidsThe APACHE II scores and SOFA scores at the day of enrolmentReceipt of mechanical ventilation (yes/no) and ventilation daysReceipt of vasopressor (yes/no), vasopressor category, and max dosesReceipt of RRT (yes/no) and RRT daysMain diagnosis at the time of admission to hospital (nervou s system disease, respiratory system disease, cardiovascular system disease, digestive system disease, urinary system disease, hematologic system disease, endocrine system disease)Complications (hypertension, diabetes, coronary heart disease, etc.)

### Handling of missing data

Of the primary outcome, data of the rate of AKI and the percentage of new receipt of RRT are not supposed to be missing for any patients. Nevertheless, some data of renal function may be missing due to protocol executive errors or record-keeping errors. Mean completer, hot deck imputation, and filling manually will be taken to minimize the effects of these missing data as much as possible. For example, if the renal function values near the missing value are in the normal range or have the same trend, the missing data will be averaged or filled with proximity. Patients without a serum creatinine measurement between enrolment and hospital discharge who survive and do not receive new RRT will be considered as not having experienced MAKE. If the patients or authorized agents give up treatment due to little chance to survive predicted by clinicians, their outcome is considered to be death. Besides, in-hospital mortality may be missing due to patients or authorized agents giving up treatment or other unpredictable accidents when the illness is not that severe. Data may also be missing due to severe adverse events (SAEs) or patients quitting the trial. Under these circumstances, an intention-to-treat analysis will be conducted to deal with the missing data. Of other outcomes, deletion will be considered if the missing data is too large to fill. Indices with complete data after conservative imputation will be included in the statistical analysis.

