### Study fluid distribution and logistics

Acetate Ringer's soution and saline administered in this trial both have different volume sizes of 250 ml and 500 ml. Components of these two crystalloids are presented (Table 2). The study is an open-label study; thus, the exact solution used is known to investigators, clinicians, and patients. Since the study is non-blind and two fluids used in this study have already been widely applied in the daily care of patients in the above ICUs, there are no problems of logistics.

**Table 2 Tab2:** Components of two crystalloids administered in the trial

Components (mmol/L)	Acetate Ringer’s solution	0.9% saline
Na	140	154
K	4	-
Mg	1	-
Ca	1.5	-
Cl	115	154
Glucose (%)	1	-
Buffer system	Acetate 25	-
Osmotic concentration (mOsmol/kg)	304	286

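### Missing renal values are to be filled with single values, partly by hand and with no masking stated, then analysed as observed; this understates uncertainty or dilutes the difference, depending on the source of the fill.

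*Protocol article*

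**What the plan says.** All of this is in the protocol article.

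- Handling of missing data expects gaps in renal function: "some data of renal function may be missing due to protocol executive errors or record-keeping errors". Three remedies are named: "Mean completer, hot deck imputation, and filling manually will be taken to minimize the effects of these missing data as much as possible".
- One worked example follows: "if the renal function values near the missing value are in the normal range or have the same trend, the missing data will be averaged". Its alternative is to take the nearest value.
- The completed data go into the analysis: "Indices with complete data after conservative imputation will be included in the statistical analysis".
- Other parts of MAKE28 have their own rules. AKI and new RRT are expected to be complete ("data of the rate of AKI and the percentage of new receipt of RRT are not supposed to be missing for any patients"). Patients whose family gives up treatment because survival is unlikely count as deaths. Patients with no creatinine measurement between enrolment and discharge "who survive and do not receive new RRT will be considered as not having experienced MAKE".
- Study fluid distribution and logistics states that "the exact solution used is known to investigators, clinicians, and patients".
- Study outcomes makes persistent renal dysfunction one of three parts of MAKE28. AKI and change in renal function are secondary outcomes.
- Sample size and statistical power frames the trial as noninferiority on an event rate of about 35%, with 156 patients per group.

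**The concern.** A single fill turns a guess into a data point. A standard test then counts it as real information, so the plan's description of the imputation as conservative can be the reverse of the truth. Where the fill borrows from both arms, the opposite damage occurs: the arms are pulled together.

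Filling by hand raises a second problem, which does not depend on how much is missing. The assigned crystalloid is recorded with the baseline data, and investigators can access the spreadsheet used for analysis (Data collection and management). Both centres give acetate Ringer's solution in odd months and saline in even months (Parallel control and allocation), so the enrolment month alone reveals the arm. Nothing stated stops the person who fills a renal value from knowing the arm.

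At stake are the renal part of the primary outcome, the AKI and renal-change outcomes, and the initial-AKI groups of the main secondary analysis.

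**Working it through.** **Inputs.** From the article: 156 per group, MAKE event rate about 35%, significance at P < 0.05 (1.96 two-sided). The article gives no share of missing renal values, so there is no plan figure to reproduce on this point. I assume a share f of 10% to 20%, missing completely at random. The 156 is taken as stated; whether it follows from the sample-size inputs is a separate question.

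**1. Mean fill within arm, one continuous renal value per patient.** The true variance of the arm mean is σ²/[n(1−f)]. The reported variance is about σ²(1−f)/n. The reported standard error is therefore (1−f) times the true one, and the real error is 2[1−Φ(1.96(1−f))].
- f = 10%: 2[1−Φ(1.764)] = 7.8%
- f = 20%: 2[1−Φ(1.568)] = 11.7%

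**2. Single hot deck within arm.** Random donors add variance, so the true variance is (σ²/n)[1/(1−f)+f], against a reported σ²/n. The real error is 2[1−Φ(1.96/√(1/(1−f)+f))].
- f = 10%: √1.211 = 1.100, giving 7.5%
- f = 20%: √1.45 = 1.204, giving 10.4%

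Simulation with 156 per arm (10,000 trials) agrees: mean fill 7.5% and 11.9%, hot deck 7.4% and 10.6%. For a binary outcome at a 35% event rate with 20% missing, multiple imputation returned the error to 4.8%.

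**3. Means or donors pooled over both arms.** The error stays near 5%, but a filled value carries no arm difference, so a true difference d becomes about (1−f)d.
- d = 15 points (35% against an assumed 20%), f = 10%: 0.9 × 15 = 13.5 (simulated 13.6)
- f = 20%: 0.8 × 15 = 12.0 (simulated 12.1)

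At f = 20% the coverage of the nominal 95% interval is 91.3%. For comparison it is 89.7% with within-arm hot deck and 94.8% with multiple imputation.

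**4. A patient's own neighbouring values (the article's worked example).** Patients stay independent of each other, so a two-sample test keeps its size. With random-walk creatinine over days 0 to 5 and 6,000 simulated trials, the error was 5.3-5.5% at 10% missing and 5.1-5.3% at 20%.

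**5. Peaks.** An average or copy of observed values cannot exceed the observed maximum, and filling deletes no observed value. The maximum after filling therefore equals the maximum before it. In simulated series with 20% of days 1 to 5 missing, about 8% of patients who truly reached 1.5 times the day-0 value were missed, with the fill and without it alike. Example: for 1.0, 1.2, (1.6 missing), 1.2, 1.0 the fill is 1.2. The peak of 1.6 is not recovered, but the fill did not remove it.

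**6. Reach into MAKE28.** Suppose 22% of patients are decided by death or RRT and 13% by the renal part. The split is assumed; only the 35% total comes from the article. Among the other 78%, the renal event rate is 0.13/0.78 = 0.167. Within-arm hot deck adds variance of [1/(1−f)+f−1] × 0.78 × 0.167 × 0.833 to 0.35 × 0.65 = 0.2275.
- f = 10%: added 0.0229, standard-error ratio √(0.2275/0.2504) = 0.953, error 6.2%
- f = 20%: added 0.0487, ratio √(0.2275/0.2762) = 0.907, error 7.5%

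Simulation gave 6.1% and 7.4%. These are upper values, because survivors with no creatinine at all fall under the no-MAKE rule and not under the hot deck.

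**The case against.** - **The only worked example is harmless to the error rate.** This stands. A reader might infer that p values are too small under the plan as a whole. The documents do not support that: it needs a fill from other patients in the same arm, and no donor pool is stated. But mean completion and hot deck are named alongside the example, and pooling the donors replaces one harm with another.
- **Creatinine peaks are not erased by filling.** This stands too. A reader might infer from "the missing data will be averaged or filled with proximity" that the method removes AKI cases. Step 5 shows that the loss comes from the missing measurement.
- **The size is unknown.** The 20% in the sample-size section is patient withdrawal, whereas renal gaps are attributed to execution and record-keeping errors. The 10% to 20% used here is an assumption and no more.
- **The effect on the primary outcome is limited.** Death, RRT and the no-creatinine case have their own rules, and the primary analysis is a mixed-effects model and not a t test. The headline error rates therefore belong to a renal value, not to MAKE28.
- **It is not stated that staff who know the arm will choose values.** The article does not say who fills by hand. What holds is that no protection is stated in a trial where the arm is known, not that filling will depend on arm.
- **An analysis plan may hold the detail.** The number of imputations and similar detail can be left there. The three methods, however, are already fixed in the text, so the fault is a stated choice and not an omission.

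**Conclusion.** The point holds in a conditional form. The article fixes single-value filling of renal values, including filling by hand with no masking stated, and analyses the result as observed. That each gap is filled with one value is inferred from the methods named; the article does not say it in words.

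| Source of fill | Real error of a nominal 5% test on a renal value (10% / 20% missing) | Effect on a true difference |
|---|---|---|
| Other patients, same arm | about 7-8% / 10-12% | unbiased, interval too narrow |
| Other patients, both arms | about 5% | 15 points becomes about 13.5 / 12 |
| Patient's own neighbours | about 5% | not assessed here; no measured peak is lost |

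The dilution in the second row favours a noninferiority conclusion if acetate Ringer's solution is truly worse, and costs power if it is truly better. MAKE28 is affected only through its renal component, with an error of about 6% to 7.5% on the assumed 22%/13% split and within-arm hot deck. All sizes rest on the assumed 10% to 20% missing completely at random. The lack of stated masking for manual filling is a weakness at any share.

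**What to change.** 1. Delete mean completion, hot deck and manual filling for every outcome value.
2. Impute the renal component of MAKE28 by multiple imputation from a pre-set model containing arm, ICU, the baseline covariates, all observed creatinine values, death and RRT, and pool by Rubin's rules.
3. Add two sensitivity runs: all missing counted as events, and all missing counted as non-events. The existing rule for survivors with no creatinine gives those patients the same value as the second run, so say which treatment they get in the main analysis.
4. Analyse daily renal values with a mixed model on the observed values.
5. Derive AKI occurrence from the same imputed creatinine series, or from observed values with the same two sensitivity runs. Without a rule here, the cases lost to unmeasured rises are not addressed.

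The cost is a revised paragraph, a little programming and slightly wider intervals. Patient care and data collection do not change.

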### Study outcomes

The primary outcome is MAKE28 (major adverse kidney events) [22]—a composite of in-hospital death, new renal replacement therapy, or persistent renal dysfunction (defined by an estimate glomerular filtration rate (eGFR) lower than 60 ml/min/1.73 m^2^ for at least 3 months [23, 24]) within 28 observational days.

Secondary outcomes will include:
The occurance of AKI which is diagnosed according to the Kidney Disease Improving Global Outcomes (KDIGO) criteria [25];Twenty-eight day mortality;Electrolyte disturbance, including hypernatremia, hyperchloremia, and hyperkalemia as well as hyponatremia, hypochloremia, and hypokalemia;Changes of renal functions based on the biomarkers measured from the participants’ plasma and urine samples collected in the first 3 days after enrolment; andOther clinical outcomes: ICU stay days, ventilator days, vasopressor days, and RRT days.

Pre-specified subgroups for primary and secondary outcome analyses will mainly include:
With or without acute kidney injury (no AKI, AKI stage 1, AKI stage 2, or AKI stage 3);With or without septic shock;Low versus high severity of sepsis: mild, moderate, and severe (classified by SOFA scores or Acute Physiology and Chronic Health Evaluation II (APACHE II) scores); andIntravenous infused volumes of the assigned crystalloids.

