### Data collection and management

Patients’ demographic data, main diagnosis, comorbidities, assigned crystalloids, general vital signs, SOFA scores, APACHE II, infection indices, and indices of multi-organ function including renal function, respiratory function, cardiac function, etc. at the time of enrolment will be collected as baseline data. Clinical information including infection indices (white blood cell count, procalcitonin, etc.), organ function indices (renal function (creatinine, urea nitrogen, cystatin C, urine volumes, etc.), respiratory function (PO_2_/FiO_2_, ventilation situation, etc.), hepatic function (total bilirubin, etc.), and indices of internal environment (blood gas analysis) will be detected during the first 5 days in ICU, and treatments such as vasopressors, mechanical ventilation, RRT, and electrolyte supplement will be recorded. These data and infused volumes of the assigned fluids will be collected for at least 5 days or until ICU discharge. ICU stay days, vasopressor days, RRT days, and ventilation days will be counted during 28 days after enrolment. These data will be collected to assess and analyze primary and secondary outcomes. Besides, patients’ blood and urine samples within the first 3 days after enrolment will be collected and stored for testing possible biomarkers for identifying AKI at an early stage.

Patients’ information and clinical data will be collected from the Hospital Information System (HIS) of the hospitals involved in this study and recorded in the Case Report Format (CRF) by the trial manager or trained personnel. An electronic password-protected excel, which will be applied for statistical analysis, will be created to summarize the data of all participants. All the data will be accessed by only investigators and authorized personnel to monitor the completeness and authenticity of the table. The confidentiality is secured and all the data will be preserved for the purpose of a secondary analysis or investigations by the investigators. To protect patients’ privacy, their names will not appear on the CRF table. Every participant will only be recognized by their study ID.

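### The missing-data rule lets secondary outcomes, or the patients lacking them, be deleted with no threshold, no unit of deletion and no blinded or prior decision

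*Protocol article*

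**What the plan says.** The protocol article's section Handling of missing data deals first with the components of the primary outcome. For gaps in renal function data it lists the filling methods: "Mean completer, hot deck imputation, and filling manually will be taken to minimize the effects of these missing data as much as possible". It then turns to everything else: "Of other outcomes, deletion will be considered if the missing data is too large to fill". The next sentence says what is analysed: "Indices with complete data after conservative imputation will be included in the statistical analysis". Among the reasons for loss it gives this: "Data may also be missing due to severe adverse events (SAEs) or patients quitting the trial". It also names giving up treatment, protocol errors and record-keeping errors.

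The secondary outcomes are fixed in advance under Study outcomes and repeated in Table 1. They include six electrolyte disturbances and "Changes of renal functions based on the biomarkers measured from the participants’ plasma and urine samples collected in the first 3 days after enrolment". Under Data collection and management, the laboratory and treatment data "will be collected for at least 5 days or until ICU discharge".

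On blinding, Study fluid distribution and logistics says: "The study is an open-label study; thus, the exact solution used is known to investigators, clinicians, and patients". On access to the data, Data collection and management says: "All the data will be accessed by only investigators and authorized personnel to monitor the completeness and authenticity of the table".

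**The concern.** This is a rule that the article states, not a detail it leaves out. Deletion is discretionary, and its trigger is the amount of missing data actually observed, so the decision can only be taken once data exist. The people holding the data know which fluid each patient received.

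The rule can be read in two ways, and for any one outcome they are alternatives:

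- If a whole outcome is deleted, a pre-listed secondary outcome can leave the report on a judgement that no one outside the team can reproduce.
- If patients are deleted, the comparison is restricted to those with values. Death, ICU discharge, withdrawal of care and serious adverse events are all related to prognosis and could differ by arm. The patients who remain are then no longer the groups that were allocated.

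**Working it through.** **What the text fixes.** Five things are needed to apply a deletion rule the same way twice.

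| Element | In the protocol article |
|---|---|
| Threshold for too much missing data | None |
| Unit deleted (value, patient or outcome) | Not stated |
| Who decides | Not stated; data held by investigators and authorized personnel |
| When, relative to sight of the arms | Not stated; open label, no blinded review described |
| Meaning of conservative imputation for these outcomes | Not stated; the named methods are written for renal function data |

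**Which outcomes are exposed.** 28-day mortality is not open to this kind of selection by survival. The section says the AKI rate should not be missing for any patient. ICU, ventilator, vasopressor and RRT days are counts over 28 days from hospital records. The 3-day biomarkers and the electrolytes remain; they need a sample or a laboratory value on a given day.

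**How large the bias could be if patients are deleted.** The plan gives no missingness figures, so this is an illustration on assumed inputs. Only the 156 per arm (Sample size and statistical power) and the 0.05 level (Statistical analysis) come from the plan. Assume:

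- the outcome z is N(0,1) in both arms, with higher values worse and no treatment effect;
- loss depends on a score equal to z plus independent N(0,1) noise;
- a fraction p with the highest scores is lost.

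Let c be the upper p point of the standard normal, φ its density, and λ = φ(c)/(1 − p). Among those retained, the mean is −λ/√2 and the variance is 1 − (cλ + λ²)/2.

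| Loss p | c | λ | Retained mean | Retained variance | Retained n |
|---|---|---|---|---|---|
| 5% | 1.645 | 0.109 | −0.077 | 0.905 | 148.2 |
| 8% | 1.405 | 0.162 | −0.114 | 0.873 | 143.5 |
| 10% | 1.282 | 0.195 | −0.138 | 0.856 | 140.4 |
| 15% | 1.036 | 0.274 | −0.194 | 0.820 | 132.6 |

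The bias is the difference in retained means. The standard error (SE) is √(variance₁/n₁ + variance₂/n₂), about 0.11 in every row. The chance of significance favouring the arm with more loss is approximately Φ(bias/SE − 1.96).

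| Loss by arm | Bias (SD) | Bias/SE | False significance, formula | Simulation of the same set-up |
|---|---|---|---|---|
| 5% v 5% | 0.00 | 0.00 | 2.5% | 2–3% |
| 5% v 8% | 0.04 | 0.34 | 5% | 4–5% |
| 5% v 10% | 0.06 | 0.55 | 8% | 8–9% |
| 5% v 15% | 0.12 | 1.06 | 18% | 18–20% |

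**A second set of assumptions.** Take an outcome correlated 0.6 with severity, deaths raised by severity, and survivors only. The two-sided error is 5.1% at 25% v 25% mortality, 5.6% at 25% v 30% (bias 0.03 SD) and 8.5% at 20% v 30% (0.06 SD). Under both sets there is no bias when loss is equal, and the bias grows with the imbalance.

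**The case against.** Four points can be made for the plan.

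1. A reader might infer that survivors-only comparisons will result, or that values go missing mainly through death. The documents support neither. No section excludes deaths, death as such is not among the named causes, and no missingness figures are given. Early discharge of recovering patients would remove better values and push the bias the other way. This stands: the biased comparison is possible, not certain, and its direction is not fixed.

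2. A reader might infer that the team will choose outcomes after seeing results by arm. The stated trigger is the amount of missing data, not the result. The outcomes are listed in advance, so a reader could notice an omission. This stands as far as intent goes. It does not supply a threshold or a decision made before the arms can be compared.

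3. The 5% v 15% case is extreme. If that loss were all deaths, mortality would be seen to differ: 0.10/√((0.05×0.95 + 0.15×0.85)/156) = 0.10/0.0335 = 2.99, and Φ(2.99 − 1.96) is about 85% power. The harmful fluid would rarely look better overall. This stands, and it is why the range is shown rather than the top figure alone.

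4. Missing-data detail usually sits in an analysis plan, which is not shown. That would answer a complaint about silence. Here the article sets out a deletion rule, and it is the stated rule that is open-ended.

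**Conclusion.** The point holds in limited form. The two sentences permit data-driven omission of a listed secondary outcome or, if patients are what is deleted, a complete-case comparison open to bias when loss differs by arm. The text does not settle which. It does not say that either will happen.

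The damage is confined to secondary outcomes, chiefly the biomarkers and electrolytes. The primary outcome and 28-day mortality are not affected by this rule. On the assumed inputs, false significance in one direction stays at 2.5% with equal loss, roughly doubles at a 3-point imbalance, reaches about 8% at 5 points and 18–20% at 10 points. These figures depend on the assumed link between loss and worse values, and on all loss acting in the same direction. The weakness in prespecification depends on neither. The change should be made, but it does not threaten the main result.

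**What to change.** Replace the two sentences on other outcomes with a rule of this kind:

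- Every secondary outcome listed under Study outcomes is analysed and reported, whatever its missingness.
- The number missing and the reason (death, ICU discharge, not measured) are given by arm for each outcome.
- Repeated laboratory and biomarker values are analysed by a mixed model on all observed values. They are neither deleted nor required to be complete.
- Values after death are treated as truncated by death, not as missing, and the comparison is shown beside mortality.
- Patients with no measurement of an outcome cannot enter its model. They are counted in the missingness table.

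A mixed model does not remove bias from loss that depends on unobserved values, so the table of reasons by arm is needed to judge what remains.

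The cost is analysis-plan wording and one table, with no new data. The downside is that some outcomes will be reported with wide intervals.
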